**7.1 Overview of Treatment Plan**

The control arm of this study will consist of induction chemotherapy (2 Cycles - Cisplatin plus continuous infusion of 5-Fluorouracil) and concurrent radiation followed by surgical resection of the esophagus. The experimental arm will consist of surgical resection followed by (if required based on final pathological staging) two cycles of chemotherapy (Epirubicin, Cisplatin and continuous infusion of 5-Fluorouracil) and concurrent extended volume radiation treatment with the last 2 cycles. Follow-up of patients with clinic visits of similar frequency to the experimental arm will be required to avoid introduction of bias in recording of time to progression.

**8.0 Surgical Treatment**

**8.1 Standardization of Technique**

All participating surgeons have agreed to follow a similar procedure. The patient's well-being and safety will always receive top priority and will be left to the individual surgeon's discretion and clinical judgement in the event of unexpected deterioration or emergency.

**8.2 Surgical Technique**

**8.2.1 Preoperative Evaluation**

All patients will undergo an evaluation to demonstrate no evidence of distant disease and no evidence of unresectable local regional invasion. A CT scan of the chest and upper abdomen, bone scan, CT scan of the head, and esophagogastroduodenoscopy are required at a minimum. A PET scan is encouraged if available and may replace a bone scan. Bronchoscopy will be done for mid esophageal tumours (< 25 cm from incisors on EGD) or if tracheobronchial invasion is suspected either clinically or on CT scan of the chest.

**8.2.2 Esophagectomy**

Esophagectomy will be performed using combined abdomen, right chest, and neck incisions for middle and upper third esophageal cancers. It is strongly recommended that the mediastinal pleura overlying the primary lesion and the mediastinal nodes and fat 5 cm proximal and distal to the primary lesion be excised en-bloc with the tumour.

Resection via the left chest or right chest and abdomen (Ivor-Lewis) may be done for mid-esophageal and gastroesophageal junction cancers. Transhiatal esophagectomy may be performed for lower third lesions. Our current standard is a minimally invasive approach (VATS and/or laparoscopic) as per tumour location and or surgeon preference.

The stomach is recommended for reconstruction, but a colon interposition may be used if technically appropriate. The anastomosis may be either stapled or sewn as per surgeon preference. A combined stapled and sewn anastomosis is recommended. Marking clips will be placed at the anastomosis if postoperative therapy is planned.

**8.2.3 Lymph Node Dissection**

At the time of esophagectomy, all lymph nodes will be removed if feasible, individually sampled and sent as separate specimens, labeled according the lymph node map. All technically accessible lymph nodes must be removed, rather than simply sampling a single representative node at each level.

**8.2.4 Proximal and Distal Margins**

Proximal and distal margins should be at least 2 cm beyond gross tumour as measured in the operating room after removal of the esophagus but prior to fixation of the specimen. Frozen sections should be obtained to ensure microscopically negative margins at the discretion of the operating surgeon. A microscopic proximal or distal margin < 1 mm will be considered positive, and the patient will remain eligible.

**8.2.5 Positive Resection Margins**

Patients that are found to have cancer positive proximal, or distal margins following preoperative chemoradiation and surgery should be considered for additional chemoradiation at the discretion of the medical and radiation oncologists. Patients in the experimental arm (postoperative chemoradiation) that were found to be T1-2 and N0 with positive resection margins should also be considered for postoperative chemoradiation.

**8.3 Surgical Quality Assurance**

**8.3.1 Completeness of Resection:** All pathology reports from patients in the study will be reviewed. Reports must contain information about gross and microscopic contamination of surgical resection margins. Tumour measurements must be recorded at surgical resection.

**8.3.2 Curative (R0):** Resections are defined as curative (complete resection: R0) when all gross disease has been removed, and microscopic examination reveals all surgical margins free of tumour, i.e., pathological stage T1-3, N0-1, M0 resected. Resections will still be considered curative if pathologic examination reveals positive lymph nodes if the gross nodes were completely resected.

**8.3.3 Palliative (R1 and R2):** Palliative resection (incomplete resection: R1 or R2) will be considered to have taken place when gross disease has been left behind (R2), or when microscopic examination reveals surgical margins which are not free of tumour (R1). Positive margins are defined as tumour at or less than 1 mm from the proximal or distal margins.

**8.3.4 No resection:** The primary tumour could not be removed.

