**3.2 Secondary Objectives**

3.2.1 To assess and compare the toxicities and morbidities of each approach.

3.2.2 To compare overall survival rates between the two treatment arms.

3.2.3 To compare recurrence in the two groups including local (gastric or esophageal bed), regional (regional lymph nodes), and distant recurrences (supraclavicular lymph node, liver, peritoneal carcinomatosis, or lung, brain, etc.).

3.2.4 To conduct an economic analysis comparing the two treatments.

3.2.5 To compare the proportion of complete (R0), microscopic positive (R1), and grossly positive (R2) resections between treatment arms.

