**5.0 Research Design and Methods**

**5.1 Eligibility Criteria**

5.1.1 Histologically documented squamous cell carcinoma or adenocarcinoma of the thoracic esophagus (> 20 cm from the incisors) or gastroesophageal junction are included. Cancers of the cervical esophagus (< 20 cm are excluded).

5.1.2 No distant metastases (M0).

5.1.3 Patients will be stratified by stage (clinical N0 versus clinical N1), and surgeon (RI versus RM versus DF)

5.1.4 Patients with tumours within 3 cm distal spread into gastric cardia as detected by esophagogastroscopy. Tumours that have > 3 cm of spread into cardia of the stomach are considered gastric cancers and are ineligible.

5.1.5 Patients with biopsy (by endoscopic ultrasound, laparoscopy, or laparotomy) proven metastatic supraclavicular nodes are ineligible.

5.1.6 Patients with biopsy proven metastatic celiac nodes are ineligible. Resectable mediastinal nodes are eligible.

5.1.7 No prior chemotherapy for this malignancy.

5.1.8 No prior radiotherapy that would overlap the field(s) treated in this study.

5.1.9 Patients with other malignancies are eligible only if > 5 years without evidence of disease or completely resected or treated non-melanoma skin cancer.

5.1.10 Age > 18 years and able to tolerate tri-modality therapy at the discretion of the treating thoracic surgeon, medical and radiation oncologists. Tumours must be resectable after assessment by the thoracic surgeon.

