**11.2 Secondary Outcomes**

**11.2.1 Survival at 5 years.** All patients will be followed every 3 months for 2 years and then every 6 months up to 5 years or until death if it occurs before 5 years. Survival will be measured from randomization.

**11.2.2 Disease Free Survival.** Recurrence rates in the two groups including local (gastric or esophageal bed), regional (regional lymph nodes), and distant recurrences (supraclavicular lymph node, liver, peritoneal carcinomatosis, or lung, brain, etc.) will be compared. Disease free survival will be measured as the time from patient entry onto study until the first malignant disease recurrence.

**11.2.3 Site of Treatment Failure.** The location of the first site of malignant disease recurrence will be recorded. Local failure occurs within the gastric or esophageal bed, or regional lymph nodes. Distant failure occurs in the supraclavicular lymph nodes, liver, peritoneal carcinomatosis, pleura, lung, bones, brain, or elsewhere not considered local.

**11.2.4 Toxicities**. Possible adverse drug or radiation events will be reported as described in the London Regional Cancer Program Patient Assessment Record (PAR).

**11.2.5 Completeness of Resection.** The number of R0, R1, R2, and unresectable patients will be compared.

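### The R0/R1 rules for the completeness-of-resection outcome disagree at exactly 1 mm, are unclear on the radial margin, and carry a stage clause that leaves clear-margin T0 and T4 specimens unplaced

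*Protocol*

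**What the plan says.** Completeness of resection is a named comparison. Protocol 3.2.5 sets the objective: "To compare the proportion of complete (R0), microscopic positive (R1), and grossly positive (R2) resections between treatment arms". Protocol 11.2.5 sets the outcome: "The number of R0, R1, R2, and unresectable patients will be compared".

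The rules for assigning a specimen stand in three places:

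- **8.2.4 (Proximal and Distal Margins):** "A microscopic proximal or distal margin < 1 mm will be considered positive, and the patient will remain eligible".
- **8.3.2 (Curative, R0):** all gross disease has been removed and "microscopic examination reveals all surgical margins free of tumour, i.e., pathological stage T1-3, N0-1, M0 resected". No distance is given.
- **8.3.3 (Palliative, R1 and R2):** R2 means that gross disease was left behind. R1 applies "when microscopic examination reveals surgical margins which are not free of tumour (R1", with no limit on which margin. The section then closes with "Positive margins are defined as tumour at or less than 1 mm from the proximal or distal margins".

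Section 8.3.4 adds a class for tumours that could not be removed. No section says which margin rule governs the outcome. Eligibility does not exclude T4 disease by stage; section 5.1.10 requires only that "Tumours must be resectable after assessment by the thoracic surgeon".

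**The concern.** An outcome that sorts patients into classes needs rules that give every specimen one class. These rules fail in three places:

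- (a) the inequality at 1 mm;
- (b) the set of margins that counts;
- (c) a restatement of R0 in terms of tumour stage, which is a different property from margin status.

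Point (c) deserves the most attention because it need not act equally on the arms. Only the control arm has chemoradiation before resection (7.1), so only there can treatment leave no residual primary tumour. A literal reader would drop such patients from the control arm's R0 count although their margins are clear. Section 17.2 states that patients, investigators and analysts are all unblinded, so the choice between readings should not be left until the data are in view.

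Margin status also enters the further-treatment passages in 8.2.5 and 10.0.

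**Working it through.** The protocol gives no rate, power or sample size for R0/R1, so there is no figure to reproduce. The check applies each written rule to five hypothetical pathology reports. Let d be the distance from tumour to the nearer of the proximal and distal margins.

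Inputs:

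- 8.2.4: positive if d < 1 mm.
- 8.3.3, last sentence: positive if d ≤ 1 mm.
- 8.3.2, margin clause: R0 if gross disease is removed and every margin is clear.
- 8.3.2 with its stage clause: as above, and stage T1, T2 or T3.
- 17.1: 48 patients planned per arm.

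| Report | 8.2.4 | 8.3.3, last sentence | 8.3.2, margin clause | 8.3.2 with stage clause |
|---|---|---|---|---|
| 1. d exactly 1 mm, radial clear, pT3 | negative | positive | R0 | R0 |
| 2. d = 0.5 mm, no tumour at the margin itself, radial clear, pT3 | positive | positive | R0 | R0 |
| 3. d = 5 mm, tumour at the radial margin, pT3 | negative | negative | not R0 | not R0 |
| 4. d = 5 mm, radial clear, pT4 | negative | negative | R0 | not R0 |
| 5. d = 5 mm, radial clear, T0 after induction | negative | negative | R0 | not R0 |

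Taking the rows in turn:

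- **Report 1.** The two distance rules contradict each other, and no reading of 8.3.2 or 8.3.3 repairs 8.2.4.
- **Report 2.** The two sections that give a distance agree. R0 results only if 8.3.2 is read without the distance sentence that follows in 8.3.3. With that sentence supplying the distance, the report is R1.
- **Report 3.** It fails R0. By the first sentence of 8.3.3 it is R1. If the last sentence is taken as the whole definition of a positive margin, it is neither R0 nor R1.
- **Reports 4 and 5.** They meet the margin clause and fail the stage clause. They are not R1 (margins clear), not R2 (no gross disease left) and not unresected. Applied literally, the stage clause leaves them without a category. Report 4 can occur in either arm; treatment-induced T0, as in report 5, only in the control arm.

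Size of one reclassification, using the planned 48 per arm:

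- one patient: 1/48 = 0.0208, or 2.1 percentage points;
- five patients: 5/48 = 0.1042, or 10.4 percentage points.

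If only resected patients are counted, the denominator is smaller and each step is slightly larger.

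**The case against.** The best defence is that one sensible reading settles most of this: tumour at any margin is R1, the 1 mm distance is an added rule for proximal and distal margins, and the stage wording is a loose gloss on a test that really concerns gross removal and clear margins. On that reading reports 2 to 5 each get one class. Clear-margin T0 and T4 specimens would have to be R0, because 11.2.5 offers no other class that fits. The outcome is also secondary, and 17.2 says that the trial is not powered for it.

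Much of this stands. It disposes of report 2 and shows that the radial problem is an ambiguity with an available answer. It does not remove the disagreement at exactly 1 mm. Nor does the protocol state that this reading is the intended one, and the stage wording is introduced as an equivalence, not as an example.

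A reader might infer three stronger things that the document does not support:

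- **That a 0.5 mm margin is a true conflict.** It is not, once the distance sentence in 8.3.3 is applied.
- **That the stage clause produces a large artefact.** Assuming that 10-30% of 48 control patients have T0 would give 4.8 to 14.4 patients and a shift of 10 to 30 points. The protocol gives no such rate, and the sum treats every randomised patient as resected. It therefore cannot support a claim that the comparison would change direction.
- **That one millimetre rule could be extended to the radial margin without extra work.** Section 8.3.1 asks for information on margin involvement, not for a measured radial distance.

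**Conclusion.** The point holds as a set of inconsistent definitions for a named between-arm outcome:

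- The 1 mm contradiction is certain, but it touches only margins reported as exactly 1 mm.
- The radial-margin rule is ambiguous: such a specimen is not R0, and it is R1 only if the last sentence of 8.3.3 is not the full definition.
- The stage clause is wrong as written. Applied literally, its T0 part would lower the control arm's R0 proportion. The net effect of the whole clause is unknown, because T4 specimens may occur in either arm.

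How many patients are affected cannot be derived from the protocol. The only size that follows from it is about 2 points per reclassified patient, on the assumption of 48 patients in the arm's denominator. The FACT-E analysis and the sample size are unaffected. The text should be corrected, but nothing here threatens the trial's main conclusion.

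**What to change.** Write one R0/R1 definition for the outcome and cite it in 8.2.4, 8.3.2, 8.3.3 and 11.2.5:

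1. Use a single inequality at 1 mm for proximal and distal margins.
2. Make R0 and R1 exact complements among specimens with all gross disease removed.
3. State that tumour at any surgical margin, including the radial one, is not R0 and counts as R1. Section 8.3.2 and the first sentence of 8.3.3 already imply this. Whether a millimetre distance also applies to the radial margin is for the sponsor to decide.
4. Delete the stage clause from 8.3.2, or extend it to any pT or ypT including T0.
5. Classify the pathology reports of both arms by this rule.

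The sponsor must also reconcile the treatment passages that depend on margin status (8.2.5 and 10.0) with the definition; which clinical rule should apply there is not judged here.

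The cost is a wording amendment. Section 8.3.1 already provides for review of every pathology report, so classification under one rule fits the existing process. Extra measurement would arise only if the sponsor chose to apply a distance to the radial margin.

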**9.0 CHEMOTHERAPY (OPIS orders: QUINTETT-ADJ or QUINTETT–NEOADJ)**

**Arm I: Preoperative Chemotherapy (Control Arm) QUINTETT-NEOADJ**

Treatment should begin within 4 weeks of randomization consisting of 2 chemotherapy cycles concurrent with radiation. Cisplatin 25 mg/m2 days 1, 2, 3, and 4 concurrent with 5FU 1000 mg/m2 / day for 96 hours continuous venous infusion, starting with the beginning of radiation therapy. Chemotherapy should start simultaneously with the first day of radiation treatment if possible, but in no circumstance later than day 5 of radiation treatment, and not earlier than on the first radiation treatment day.

This regimen is repeated at week 5 of radiation therapy.

**Arm II: Postoperative Chemotherapy (Experimental Arm) QUINTETT-ADJ**

Treatment should begin between 8 to 12 weeks following surgery.

The chemotherapy treatment is as follows:

Chemotherapy alone for 2 cycles – One cycle consists of Epirubicin 50 mg/ m2 and Cisplatin 60 mg/m2 day 1, and 5-Fluorouracil (5FU) by continuous venous infusion at 200 mg/m2 for 21 days.

Chemotherapy (concurrent with radiation) immediately afterwards for 2 additional cycles – One cycle consists of Cisplatin 60 mg/m2 day 1, and 5-Fluorouracil (5FU) by continuous venous infusion at 200 mg/m2 for 21 days. Concurrent radiation is to start on the same day as cisplatin is administered if possible, but in all cases within 3 days before or after that date.

Details regarding the chemotherapeutic agents:

**9.1.1 Availability**

Cisplatin is commercially available as a sterile lyophilized powder in 10 mg and 50 mg vials when dissolved in 10 ml and 50 ml of sterile water respectively for injection (1 mg / ml). It is also available in an aqueous solution (Platinol-AQ7) with a concentration of 1 mg / ml in 50 and 100 mg vials. Do NOT use aluminum needles or aluminum containing IV sets. Further dilute the desired dose in a least 100 ml (500 ml to 1 liter is preferred) of 0.9% sodium chloride (NS) for infusion.

**9.1.2 Storage and Stability**

Unopened vials are stable for 2 years, Reconstituted vials are stable for 20 hours at room temperature, or for 72 hours if reconstituted with bacteriostatic water. DO NOT REFRIGERATE cisplatin solutions, as it will precipitate.

**9.1.3 Administration**

Preoperative chemotherapy: Cisplatin 25 mg/m2 bolus IV (in a 250 mL bag) infusion over 30 minutes on days 1, 2, 3, and 4 with prehydration, other standard renal-protective measures, and appropriate antiemetic coverage. The following is recommended:

Prior to cisplatin, begin intravenous hydration with 500 mL normal saline IV over 1 hour. Furosemide 40 mg IV in a 50 mL mini bag with hydration. After the cisplatin infusion, complete 250 ml of normal saline IV hydration over 30 minutes.

Postoperative chemotherapy: Cisplatin 60 mg/m2 bolus IV (in a 500 mL bag) infusion over 1 hour on days 1, 22, 43, and 64 with prehydration, other standard renal-protective measures, and appropriate antiemetic coverage. The following is recommended:

Prior to cisplatin, begin intravenous hydration with 1,000 mL normal saline IV over 2 hours. Furosemide 40 mg IV in a 50 mL mini bag with hydration. After the cisplatin infusion, complete 500 ml of normal saline IV hydration over 1 hour.

Anti-emetics include dexamethasone 4 mg po q12h starting the morning of the first dose of chemotherapy and continuing for 5 doses after the last cisplatin dose of each cycle; ondansetron 8 mg po q12h starting the morning of the first dose of chemotherapy and continuing for 5 doses after the last cisplatin dose of each cycle; prochlorperazine 10 mg po q4h prn.

The patient should be encouraged to drink as much liquid as possible overnight. Needles, syringes, catheters or IVC administration sets containing aluminum parts should not be used, as contact with cisplatin yields a black precipitate.

**9.1.4 Toxicities**

Cisplatin most commonly causes myelosuppression, nausea and vomiting, diarrhea, alopecia, renal toxicity, electrolyte wasting (e.g., potassium, magnesium, phosphate, calcium), peripheral neuropathies, and ototoxicity (high frequency hearing loss, tinnitus). Less commonly, hypersensitivity reactions, severe myalgias and neuropathies, optic neuritis, hyponatremia, elevated liver enzymes, and hyperuricemia may occur.

**9.1.5 Drug Interactions**

Concomitant administration with other nephrotoxic or ototoxic drugs, such as aminoglycosides, amphotericin B, furosemide, and methotrexate, increases the risk of renal failure and / or hearing loss. Decreased phenytoin levels have been observed when cisplatin is given with phenytoin therapy.

**9.2 5-Fluorouracil (5-FU, fluorouracil, Efudex7, Adrucil7)**

**9.2.1 Availability**

5-FU is commercially available and is an antimetabolite that interferes with RNA and DNA synthesis. Fluorouracil injection (Roche Laboratories): 50 mg / ml, 10 ml vials; clear, yellow, aqueous solution; Fluorouracil (Cetus, Lyphomed, Americal): 50 mg / ml; 10 ml, 20 ml, 100 ml vials, 10 ml ampules; Fluorouracil (Solopak): 50 mg / ml, 10 ml ampules.

**9.2.2 Preparation**

Inspect for precipitate; if found, agitate, or gently heat in water bath. Filter ampules with aspiration needle (5 μm). Compatible with D5W, 0.9% NS, D5LR.

Additive incompatibility: carboplatin, cisplatin, cytarabine, diazepam, doxorubicin, droperidol, epirubicin.

Y-site incompatibility: filgrastim, ondansetron, vinorelbine, dexamethasone.

**9.2.3 Storage and Stability**

Store at room temperature and protect from light. Dark yellow color indicates decomposition. Stable in polypropylene syringes. Stable in PVC reservoirs for infusion pump for 12 days. May adsorb to glass surfaces. Stable in cellulose nitrate / acetate ester or Teflon filters.

**9.2.4 Administration**

Postoperative chemotherapy: 5-Fluorouracil 200 mg / m2 / day continuously for 4 cycles of 21 days each, with cisplatin and epirubicin on days 1 and 22, and cisplatin on days 43 and 64 as indicated under 9.1 above. The CIV 5FU will thus continue for a total of 12 weeks, barring dose adjustments due to toxicities.

5-FU will be administered intravenously by continuous infusion through a Percutaneous Intravenous Central Catheter (PICC), or other central line, using a standard mechanical or electrical pump.

Preoperative chemotherapy: 5-Fluorouracil 1000 mg / m2 / day continuously for 4 days (96 hours) concurrently with radiation, and together with cisplatin daily (see above). This cycle is repeated starting with the 5th week of radiation therapy.

**9.2.5 Toxicity**

Nausea, vomiting (mild); ileus; diarrhea; stomatitis: 5-8 days after treatment initiation; gastric ulceration; myelosuppression: leukopenia, granulocytopenia (9-14 days); thrombocytopenia (7-14 days); alopecia; loss of nails; hyperpigmentation; photosensitivity; maculopapular rash; palmar-plantar erythrodysethesias: (42-82% receiving continuous infusion); CNS effects: disorientation, confusion (rare); cardiotoxicity; myocardial infarction, angina, asymptomatic S-T changes 68%; ocular effects (rare).

**9.2.6 Drug Interactions**

Leucovorin and other reduced folates enhance toxicity of 5-FU. Vitamins with large amounts of folic acid should be avoided.

